#### Primary outcome

The primary outcome measure is use of a LARC (IUD or sub-dermal implant) at 4 months post-MR. Participants will be considered ‘LARC users’ if they report having a sub-dermal implant or IUD inserted at the 4-month follow up interview. The 4-month time point was selected to enable us to establish any effect of the intervention on continuation of the injection (effective for 3 months) and pills (clinics usually dispense 3 months-worth of pills).

#### Secondary outcomes

Secondary outcome measures include current use of any effective modern contraceptive method at 2 weeks, 4 and 12 months post MR. We define modern contraceptive methods according to the WHO as those associated with <10% 12 month pregnancy rates [13]. These will be measured as having had or having a partner who has had sterilization, currently have a sub-dermal implant or an IUD inserted, have received the injection in the last 3 months, currently using the contraceptive pill and reporting that they always or usually take the pill on time. Further secondary outcomes are self-reported pregnancy at the time of the four and 12 month interviews, having had an MR since enrolment into the study and having experienced violence since enrolment. Data from the contraceptive calendar will be used to estimate a point prevalence of contraceptive use at any given time and contraceptive discontinuation rates.

#### Hypothesized intermediate outcomes

At 4-months, data will be collected on the following hypothesized intermediate outcomes: satisfaction with family planning method, frequency of communication about family planning with husband and with in-laws, knowledge and attitudes towards family planning and self-efficacy to use contraception.

#### Dose

The effect of the dose of the intervention on the primary outcome will be examined using self-reported information on intervention use (listened to none, some or all of the messages), spoke to a call centre counsellor (yes/no).

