Each participant will be sent a series of 11 automated, interactive voice messages sent to their mobile phone over a 4-month period, starting within a week of the MR procedure. Messages will be sent weekly for the first 6 weeks and fortnightly for the following 8 weeks. The recorded messages, which are free to receive, start playing when the phone is answered and are delivered through a secure online platform from ‘I Am Digital’ in Dhaka. If the call is not answered it is re-sent after 30 min and again after another 30 min. At the end of each of the 11 messages, the recipient can press keys one to five to select one of the following options: (1) repeat the message; (2) listen to one or more of seven additional messages, one about each modern method of contraception (condoms, pills, injectable, implant, IUD, male and female sterilization); (3) speak to a call centre counsellor; (4) report that they are fine and don’t need further information today or (5) opt out from receiving further messages. At recruitment, the participant is asked to select one of five time slots for receiving the messages. The content of the 11 messages is tailored to the individual’s chosen method as follows: the method of contraception received at the clinic is used to allocate participants to one of six message groups: no method users, condom users, pill users, injectable users, implant users and IUD users. Seven core messages will be sent to all participants reminding them of the benefits of using contraception, addressing key barriers such as fear of infertility and addressing information gaps, particularly around LARC and permanent methods. The remaining four messages will be specific to the method group for example, pill users will receive the seven core messages plus four messages tailored to supporting pill use. For current contraceptive users, the tailored messages provide information and support for continuation and correct use of their chosen method, they also aim to promote safe-switching among women who are not happy with their method. The tailored messages sent to non-users are designed to encourage uptake of contraception. Women are reminded at recruitment and in the messages to inform the call centre counsellor if they switch contraceptive methods. The messages do not mention MR or refer to the participant’s clinic visit to prevent their MR status being disclosed should someone else answer or overhear the call.

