### Data collection

Data collection tools will be developed in English then translated into and administered in Bangla. Where possible we will use or adapt existing tools including questions from the Bangladesh Demographic Health Survey [25]. On the first day of recruitment, data on the family planning services available at participating facilities will be collected from the facility manager or MR provider using a questionnaire administered by an RA (following informed consent). Study participants will be interviewed by the recruiting RA after enrolment to collect data on demographics (poverty level will be measured using the Progress out of Poverty Index (PPI)), reproductive history and intentions, the current MR and any family planning counselling and methods received, household decision making, experience of violence, type and frequency of mobile phone usage, contact phone number and preferred time of day to receive messages and to be contacted for follow up interviews.

Female RAs based at the MSB head office will administer follow-up questionnaires by telephone. The 2-week interview lasting approximately 5 min will ask about current contraceptive use. Changes in contraceptive method among intervention participant will be made in the online platform administering the messages. The 4-month and 12-month questionnaires will last approximately 15 min and will ask about marital status, fertility intentions, experience of violence, contraceptive use in the preceding months/weeks, any pregnancies or MR procedures, contraceptive discontinuation and reasons for stopping a method. Information on side effects will be collected where it led to discontinuation of a method. The 4 and 12 month follow up survey questions will be the same except that the time frame for some questions will differ and the 4-month survey will include measurement of hypothesised intermediate outcomes and questions to assess use of and satisfaction with the intervention and any related privacy concerns. Questions on the outcome will be asked at the start of the interview, prior to questions about the intervention.

All contraceptive use and non-use since baseline will be recorded using a modified version of the Demographic and Health Survey contraceptive calendar [25]. Participants will be asked at recruitment whether they consent to the study team accessing their clinic records to verify reports of MR procedures and LARC insertions or removals.

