#### Use of the intervention

Data on use of the intervention such as whether recorded voice messages are listened to and whether clients interact with the messages will be generated by the mHealth platform. Calls to the call centre will be monitored; call centre operators will complete a standard form for every caller to collect basic information on who the caller is (participant themselves, husband, friend etc.) and the reason or reasons for the call. A small number of calls will be audio recorded.

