Contraceptive discontinuation rates will be estimated over the one-year project period using Kaplan-Meier curves, overall and by family planning method. The log-rank test will be used to test for differences in discontinuation rates between methods. Table 1 summarizes the method of analysis for the primary and secondary outcomes. We will use Stata to conduct data analysis [24]. Data on use of the messages and details of calls made to the call centre will be analysed descriptively. Sub group analysis will be conducted to explore whether the intervention effect varies according to age, education, SES, type of MR procedure (medical vs surgical), experience of violence in the last year (yes/no), and on who makes decisions about whether the participant uses contraception (self/self and one or more other person/other person).

Transcripts from the calls to the call centre will be analysed qualitatively to examine the type of information and/or support the counsellors provide to enable a more detailed description of the intervention.

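### The dose analysis relies on recalled use although platform and call-centre records exist, and it calls a self-selected comparison an effect

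*Protocol article*

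**What the plan says.** The Dose section of the protocol article reads: "The effect of the dose of the intervention on the primary outcome will be examined using self-reported information on intervention use". It then names two exposures: "listened to none, some or all of the messages), spoke to a call centre counsellor (yes/no".

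The section Use of the intervention describes two other sources. Data on "whether recorded voice messages are listened to and whether clients interact with the messages will be generated by the mHealth platform". For telephone contact, "call centre operators will complete a standard form for every caller to collect basic information on who the caller is", and the form also records why the person rang.

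The Data analysis section limits what is done with these: "Data on use of the messages and details of calls made to the call centre will be analysed descriptively".

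The Data collection section says when recalled use is obtained: "the 4-month survey will include measurement of hypothesised intermediate outcomes and questions to assess use of and satisfaction with the intervention". It adds a safeguard on order: "Questions on the outcome will be asked at the start of the interview, prior to questions about the intervention". The Intervention section shows that the amount received is partly the woman's own choice, since the key options after each message include "3) speak to a call centre counsellor; (4) report that they are fine and don’t need further information today or (5) opt out from receiving" (the last of these ends the calls).

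**The concern.** There are two distinct problems, and they need different remedies.

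**Measurement.** The exposure is a three-level recollection of 11 calls spread over about four months. It is given by the same respondent, in the same interview, as the self-reported outcome. Random recall error would dilute a real gradient. If women who have just reported a LARC also tend to report more listening, a gradient can appear from nothing. A source that does not depend on memory is already being collected.

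**Interpretation.** Women decide whether to answer, whether to press through to a counsellor and whether to opt out. A woman who already wants an implant or IUD may well engage more. A comparison across dose levels is therefore observational, and the article's wording presents it as an effect.

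The article's Discussion asks whether automated content can replace counsellor time and remain effective. The dose analysis is the stated analysis closest to that question, so a biased counsellor association could mislead decisions about scale-up.

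**Working it through.** **Inputs from the article (Sample size).** LARC use 9.4% in control and 16.4% in intervention, significance level 0.05, power 80%, 714 women, 960 after allowing for 25% loss.

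**The plan's own figure.** With unpooled variance and a two-sided test, n per arm = (1.960 + 0.842)² × (0.094×0.906 + 0.164×0.836) / 0.07² = 7.849 × 0.2223 / 0.0049 = 356.03. This rounds up to 357, or 714 in total, as stated. Then 714/0.75 = 952, consistent with at least 960. The article gives no figure for the dose analysis. It also gives no recall accuracy and no rate of intention to use a LARC, so everything below rests on assumed values shown as ranges.

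**(a) Recall error unrelated to outcome.** Assume half the intervention arm are high listeners and the whole gain falls on them. Their rate is (0.164 − 0.5×0.094)/0.5 = 23.4%, against 9.4% in the rest, a true difference of 14.0 points (risk ratio 2.49). With half exposed and sensitivity equal to specificity (s), observed difference = (2s − 1) × 14.0.

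| s | Observed difference | Observed risk ratio |
|---|---|---|
| 0.9 | 11.2 points | 2.04 |
| 0.8 | 8.4 points | 1.69 |
| 0.7 | 5.6 points | 1.41 |

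The pattern is the same with other shares of high listeners. At 30% the true 23.3 points becomes 17.5, 12.5 and 8.0. At 70% the true 10.0 points becomes 7.5, 5.3 and 3.4.

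**(b) Recall error related to outcome, no true dose effect.** Assume 50% of non-users of LARC report listening, and 60, 70 or 80% of users do. Odds ratio = [p/(1 − p)] / [0.5/0.5], giving 1.5, 2.3 and 4.0.

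**(c) Confounding by intention, no true dose effect, exposure measured perfectly.** Keep overall LARC use at 9.4%. Let a share π intend a LARC and be R times as likely to obtain one, so the rate in the others is 0.094/(πR + 1 − π).

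- *Listening:* π 10 to 30%, R 3 to 5, intenders listening 60 to 80% against 50%. The odds ratio runs from 1.07 to 1.74. At the upper end (π = 0.3, R = 5, 80% against 50%) the rates are 0.0427 in others and 0.2136 in intenders. LARC use is (0.24×0.2136 + 0.35×0.0427)/0.59 = 11.2% in listeners and (0.06×0.2136 + 0.35×0.0427)/0.41 = 6.8% in non-listeners.
- *Counsellor contact:* π 10 to 20%, R 3 to 5, intenders calling 20 to 30% against 5%. The odds ratio runs from 1.43 to 2.33.

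Logs would remove recall error as in (a) and (b). They would do nothing about (c).

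**(d) Baseline use.** The 9.4% is derived from method uptake at the procedure. If those women all continue, 9.4/16.4 = 57% of the LARC users expected in the intervention arm had their device before any message was sent. Baseline LARC use therefore has to be in any dose model.

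**The case against.** **Points that stand.** The logs are imperfect. The Intervention section itself foresees someone else answering or overhearing the call. The article does not say that the platform records a message as heard to the end, or that call forms carry the participant ID, and callers may be a husband or friend. Self-report at least asks the woman herself. Asking outcome questions first, verifying LARC insertions against clinic records with consent, and cross-checking calendar data all protect the outcome report, though none makes the later exposure report independent of it. Dose is not among the listed primary or secondary outcomes. The article states no dose model, and its detail may properly sit in an analysis plan that is not shown. The choice of source and the word effect, however, are stated.

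**Stronger readings the documents do not support.**

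- A reader might infer that recall causes the confounding. It does not: self-selection after randomisation does, and it would remain with perfect logs.
- A reader might infer a very large false association. If 50% of women who obtain a LARC had phoned against 10% of others, the odds ratio is (0.5/0.5)/(0.1/0.9) = 9. That is a single assumed scenario which fixes calling by outcome status and contains no recall error. The counsellor scenarios in (c) give 1.43 to 2.33.
- A reader might infer that logs recover the 480 × 0.25 = 120 intervention women expected to be lost. Those women also lack the 4-month outcome, so logged dose helps there only through imputation.

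**Conclusion.** The concern holds as two separate points. First, the article chooses the weaker exposure source over one already collected. Recall error can dilute the dose association (14 points to about 6 to 11) or inflate it (odds ratio 1.5 to 4.0 from no effect). Second, the comparison is self-selected and should not be called an effect; intention alone can give an odds ratio of about 1.1 to 2.3, whichever source is used. All these sizes depend on assumed inputs and show plausible scale only. They are not estimates for this trial. The consequence is confined to an exploratory analysis.

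**What to change.** 1. Define message dose mainly from the platform log, as the number of the 11 messages answered, or heard to the end if the platform records that. Take counsellor contact from the call-centre forms where they can be linked to the participant. Keep self-report as a cross-check and report agreement.
2. Adjust for baseline LARC use, and say which arm or arms enter the counsellor analysis, since control women can also ring the centre.
3. Report the result as an association, replacing the word effect in the Dose section.
4. If a causal statement is wanted, add a complier analysis with randomised arm as the instrument and a low threshold, such as any message heard. State the exclusion restriction: allocation changes LARC use only through crossing that threshold. A high threshold strains it. If 80% reach the threshold and the other 20% get half the effect (assumed), the estimate is (0.8 + 0.2×0.5)/0.8 = 1.125 times the truth.

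The cost is the linkage work and, if step 4 is used, one extra model with a wider interval than the naive comparison. Uncertainty about who answered the phone remains and should be acknowledged as a limitation.

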### Sample size

Sample size calculations were based on the primary outcome: LARC use 4 months after the MR procedure. Based on approximately 28,000 MR procedures conducted between November 2011 and June 2013 in government facilities supported by Ipas and approximately 16,500 in MSB clinics between October and December 2013, 7.0% of women are expected to select an IUD as their post-MR contraceptive method and 2.4% an implant, resulting in an expected 9.4% LARC uptake at baseline. A similar mHealth trial in Cambodia saw LARC use at 4 months increase from 9% to 29% with receipt of the intervention. Given the low cost of sending automated phone messages, a smaller increase may be programmatically important. To detect an absolute increase in LARC use of 7%, from 9.4% in the control group to 16.4% in the intervention group (a relative risk of 1.74), at four-month follow-up with a 0.05 significance level and 80% power, and assuming equal numbers of women in intervention and control groups the study needs a minimum of 714 participants. We increased this to a minimum of 960 to allow for 25% loss to follow-up (Fig. 1).

**Fig. 1 Fig1:**
[figure not shown]
Study design and participant timeline

### Data management

The questionnaires will use anonymous ID numbers to identify respondents in the analysis. They will be composed of one digit to identify the clinic type (MSB/Ipas), followed by two digits for the facility code followed by a unique client identifier, composed of the day, month, staff member code and client number. An example of this could be M 01 2804 02 03. M indicates it is an MSB facility, 01 is the facility code. Two thousand eight hundred four is the date of the enrolment, 02 indicates the staff member code within the clinic and 03 indicates that it is the 3rd client enrolled on that day.

Study consent forms and baseline questionnaires will be photocopied at the facility. One copy will be posted to a central office for entry and storage, the other copy will be stored securely at the facility or in a locked location at the home of the research assistant until it can be collected in person by the research team. Two-week, 4 and 12 month questionnaires will be stored securely in a locked cabinet at MSB and the data entry company head offices in Dhaka. To protect women’s confidentiality, data will be recorded using numeric study identifiers, and all data (both hard copy and electronic) will be stored under the study identifiers and kept in locked file cabinets and password protected files, respectively. Data entry will be done in Microsoft Access by an external data entry specialist, and at least 10% will be double-entered. After entry, data will be checked for consistency and completeness. Data on contraceptive use will be cross-checked between time points, for example contraceptive calendar data collected at 4 months will be cross checked with baseline and 2-week data. Data will be checked for incompatible responses, for example being pregnant and using a method of contraception at follow-up*.* The data will be cleaned, analysed, and findings will be written up, by the principle investigators and researchers at Marie Stopes, Ipas and The London School of Hygiene and Tropical Medicine. Only the researchers conducting follow up surveys and those entering and checking data will have access to participant contact details. Audio recordings of calls to the call centre will be transcribed and translated into English.

### Training and monitoring

Research Assistants enrolling participants into the study and collecting baseline data will attend a 5-day training in Dhaka led by one international and one local investigator. Five supervisors will be trained to conduct supervision visits to ensure study protocols are being followed. Supervisors will be given a checklist to complete at each visit. Regular monitoring visits will be made by the study manager during enrolment and data collection to ensure study protocols are being followed and to identify any problems with recruitment or data collection. If necessary, further guidance or training will be provided to data collectors. Research Assistants conducting follow-up surveys will receive up to 5 days training (dependent on whether they have previous involvement in the study). Follow up data collection will be monitored by the study manager during daily de-briefs.

No data monitoring committee will be established for this trial as the likely risks to participants of receiving an mHealth intervention are known to be minimal. All adverse events reported to the study team during follow up surveys or via calls to the study or call centre numbers will be reported by the study manager to the principal investigator within 1 week of their occurrence. The response will be agreed with the other study investigators and where appropriate reported to the ethical committees.

The protocol and intervention were reviewed by an in-country advisory committee who will meet intermittently to review progress and give input. The committee includes the Director of Primary Health Care and Director of Continued Medical Education at the Directorate General of Health Services; the Director of Maternal and Child Health services and the Director of Information, Education and Motivation at the Directorate General of Family Planning; Executive Director, Reproductive Health Services, Training and Education Programme (a non-governmental organisation working in Government of Bangladesh Hospitals); Director, Bangladesh Association for Prevention of Septic Abortion; President, Obstetric and Gynaecological Society of Bangladesh; Country Director, Population Council; Chief Executive Officer, Bangladesh Centre for Communication Programme; Senior Director, Marie Stopes Bangladesh; Country Director, Ipas Bangladesh.

### Data analysis

We will adhere to the CONSORT guidelines for reporting RCT conduct and outcomes. Intention-to-treat principles will be used for primary outcome analysis, meaning all participants will be analysed according to the arm to which they were randomised. We will investigate the patterns of missing data, and will report any treatment group imbalances between those who do and do not complete the study.

The primary analysis, using multiple imputation to handle missing data (as detailed below), will be a logistic regression of 4-month LARC use on treatment and baseline use. For the primary analysis, we assume data are missing at random, given treatment group, 2-week and baseline LARC use, baseline socio-economic status (SES) and age. Under this assumption, multiple imputation of missing 4-month data will be performed separately for the two intervention groups, by full conditional specification, using the following variables: baseline, 2-week and 4-month LARC use, together with auxiliary variables, baseline SES and age. The multiple imputation procedure will also impute any missing baseline data (under the same assumption). One hundred imputed datasets will be created, and the imputation process will be checked for convergence and perfect prediction.

The primary analysis will be validated by an analysis under the slightly stronger assumption that data are missing at random, given treatment group, baseline LARC use, baseline SES and age. This can be achieved with a logistic regression of 4 month LARC use on baseline LARC use, intervention group, baseline SES and age. Robustness of inference from the primary analysis to the missing at random assumption will be explored using the “δ -method” for information-anchored sensitivity analysis [26].

Keeping the information in the data constant, this method allows us to explore the robustness of our conclusions about treatment to the missing at random assumption (MAR). In this study, MAR assumes that — among patients in the same treatment group, with similar baseline data and similar early follow-up — the odds of LARC use at the end is the same whether or not their data are missing. This assumption is untestable, so the “δ -method” explores how the conclusions vary as — still among patients in the same treatment group, with similar baseline data and similar early follow-up — the odds of LARC use at the end differs by δ between patients with observed and missing data.

Contraceptive discontinuation rates will be estimated over the one-year project period using Kaplan-Meier curves, overall and by family planning method. The log-rank test will be used to test for differences in discontinuation rates between methods. Table 1 summarizes the method of analysis for the primary and secondary outcomes. We will use Stata to conduct data analysis [24]. Data on use of the messages and details of calls made to the call centre will be analysed descriptively. Sub group analysis will be conducted to explore whether the intervention effect varies according to age, education, SES, type of MR procedure (medical vs surgical), experience of violence in the last year (yes/no), and on who makes decisions about whether the participant uses contraception (self/self and one or more other person/other person).

Transcripts from the calls to the call centre will be analysed qualitatively to examine the type of information and/or support the counsellors provide to enable a more detailed description of the intervention.

